### Sample Size

To determine the sample size, we assumed a type I error of 0.05 and a type II error of 0.20 (80% power). The calculation was based on a minimum detectable difference of 1.5 points in pain intensity measured using the numerical rating scale (NRS). This minimum difference aligns with established minimal clinically important difference values for the NRS in breast cancer–related pain contexts, which range from 1.39 to 2.0 points [30-33].

An estimated SD of 2.61 was selected based on a conservative approach considering the variability reported in breast cancer populations using the NRS, where SDs range from 1.4 to 2.8 [34-37]. This conservative estimate ensures adequate statistical power even if data dispersion is greater than anticipated. Considering an estimated 10% dropout, the required sample size was 108 women, with 54 allocated to the control group (CG) and 54 allocated to the intervention group (IG). The power calculations were performed using the GRANMO online program (version 7.12; Programa de Registre Gironí del Cor).

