### Randomization, Allocation, and Blinding

The participants in the study will be randomly assigned to 1 of 2 groups: the IG (MI+AO+mobility exercises) or the CG (mobility exercises alone). All the participants will perform mobility exercises of the upper limb involving flexion, extension, abduction, adduction, internal rotation, and external rotation for approximately 20 minutes between 1 and 3 times a day 3 times a week for the duration of the intervention (6 weeks).

The randomization process will be carried out using the Research Randomizer tool and an allocation ratio of 1:1 with the aim of guaranteeing impartiality and validity in the study and ensuring a balanced distribution, simple randomization, and a reduction in biases while preserving the integrity and reliability of the results. The randomization list will be created by a member of the research team without contact with participants or access to personal or clinical information.

This is a single-blind study, as neither participants nor the researchers delivering the intervention can be blinded. Blinding will be maintained for the researchers responsible for collecting outcome data, administering evaluation instruments, and performing the statistical analyses.

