### Data Analysis

First, a descriptive analysis of all study variables will be performed. Continuous variables will be summarized using means and SDs (or medians and IQRs), and categorical variables will be summarized using frequencies and percentages.

The normality of outcome distributions will be assessed for each study group and time using the Kolmogorov-Smirnov test with Lilliefors correction. If normality assumptions are not satisfied, equivalent nonparametric approaches will be considered.

Baseline comparability between groups will be assessed using a 2-tailed Student *t* test (or Wilcoxon rank-sum test if normality is not met) for continuous variables and chi-square or Fisher exact tests for categorical variables.

Second, inferential analyses will be carried out following an intention-to-treat approach whereby all randomized participants will be included in the analyses focused on between-group comparisons (intervention vs control) based on pretest-posttest change scores. Missing data will be imputed and included in all analyses.

The primary analysis will consist of evaluating the effect of the intervention on pain at T0, T1, and T2 comparing changes between the IG and CG from baseline using a linear mixed-effects model.

For all outcome variables meeting normality assumptions, longitudinal trajectories will be evaluated using linear mixed-effects models with participant-specific random intercepts for within-subject correlation. The models will include fixed effects for group (control vs intervention), time (baseline, T1, and T2), and the group × time interaction. Standardized effect sizes (Cohen *d*) will be calculated from the adjusted between-group differences in change from baseline estimated by the mixed-effects models. Effect size will be interpreted as very small for values of less than 0.20, small for values of 0.20 to 0.49, moderate for values of 0.50 to 0.79, and large for values of 0.80 or more.

For variables not meeting normality assumptions, appropriate nonparametric methods will be considered. Between-group comparisons of change scores at each follow-up will be performed using the Wilcoxon rank-sum test.

In all cases, the significance level will be set at .05. The data will be analyzed using the SPSS program (version 27; IBM Corp).

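### The random intercept in the primary mixed model ties the standard error of the T1 pain effect to a variance pooled over all visit pairs; an unstructured covariance over the three visits would remove that assumption at almost no cost

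*Protocol article*

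**What the plan says.** The Data Analysis section specifies a linear mixed-effects model for pain, with fixed effects for group, time as three categories, and their interaction. Dependence between a woman's measurements is handled by "participant-specific random intercepts for within-subject correlation". The section names no residual covariance structure, no alternative structure and no robust standard error. On incomplete data it says "Missing data will be imputed and included in all analyses", without naming a method.

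The Data Collection section makes pain the primary outcome and T1 (6 weeks) the primary time point. It places T2 three months after the 6-week intervention ends.

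The Sample Size section uses a "minimum detectable difference of 1.5 points in pain intensity" and states "An estimated SD of 2.61 was selected". It does not say whether that SD belongs to a single visit or to a change score.

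**The concern.** A random intercept with independent, equal-variance residuals implies compound symmetry: equal variances at the three visits and equal correlations for the three visit pairs. There are three reasons to doubt this here:

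- The T0–T1 interval contains the whole treatment period, and the T1–T2 interval contains none of it.
- The intervals differ. T0–T1 is 6 weeks and T0–T2 is about 19 weeks. Even if T2 were counted as 3 months from baseline, as the Intervention and Control Condition sections could be read, T0–T2 would span about twice the T0–T1 interval.
- The pain scale is bounded at 0 and the eligibility criteria set no minimum pain, so variances may change as women approach the floor.

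If compound symmetry fails, the confidence interval and p-value for the primary T1 contrast rest on the wrong variance. The test is too liberal if T0–T1 is the weakest pair or T1 the most variable visit. It is too conservative if correlation decays with time.

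**Working it through.** **The plan's own figure.** Inputs from the Sample Size section are difference 1.5, SD 2.61, alpha 0.05, power 80% and 10% dropout. A two-sided test is taken because a one-sided one gives 38 per arm and does not fit.

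- n per arm = 2 × (2.61 × (1.960 + 0.842) / 1.5)² = 47.5, so 48.
- 48 / 0.9 = 53.3, so 54 per arm and 108 in total.

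The stated 108 is reproduced, and nothing below changes it.

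**What the model uses.** With complete data and a saturated group × time term, the T1 effect is the difference between arms in mean T0-to-T1 change. With n per arm:

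- Correct SE² = (2/n) × Var(T1−T0).
- Random-intercept SE² = (2/n) × the mean of Var(T1−T0), Var(T2−T0) and Var(T2−T1).

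A REML fit to one simulated data set (54 per arm, correlations .7/.4/.6) confirmed this. The fitted SE was 0.4825, equal to the closed form. The T0–T1 changes alone gave 0.380. The point estimate was −0.314 both ways.

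**Size.** With equal variances, the ratio of model SE to correct SE is √[(1 − mean r) / (1 − r01)], and type I error is 2 × [1 − Φ(1.96 × ratio)]. For .4/.4/.7 the ratio is √(0.5/0.6) = 0.913, and 2 × [1 − Φ(1.789)] = 7.4%. The correlations are assumptions. The SEs take 2.61 as the SD at each visit, with 54 per arm.

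| Assumed r (T0–T1 / T0–T2 / T1–T2) | Model SE | Correct SE | Ratio | Type I error |
|---|---|---|---|---|
| .5 / .5 / .5 | 0.502 | 0.502 | 1.000 | 5.0% |
| .4 / .4 / .7 | 0.502 | 0.550 | 0.913 | 7.4% |
| .4 / .35 / .7 | 0.511 | 0.550 | 0.928 | 6.9% |
| .6 / .4 / .6 | 0.485 | 0.449 | 1.080 | 3.4% |
| .7 / .4 / .6 | 0.468 | 0.389 | 1.202 | 1.9% |

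Unequal variances act in the same way. With SDs 2.0/2.8/2.0 and all correlations .5, the change variances are 6.24 (T1−T0), 4.00 (T2−T0) and 6.24 (T2−T1), mean 5.49. The ratio is √(5.49/6.24) = 0.938 and type I error is about 6.6%.

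**Power in the conservative direction.** For .6/.4/.6 with 48 per arm:

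- Change SD = 2.61 × √0.8 = 2.33, and SE = 2.33 × √(2/48) = 0.476, so 1.5/0.476 = 3.15.
- Power with the correct SE is Φ(3.15 − 1.96) = 88%.
- Power with the model SE is Φ(3.15 − 1.96 × 1.080) = 85%.

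For .7/.4/.6 with 54 per arm the figures are 97% and 93%.

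**Imputation (conditional).** If 10% of values are filled in once and counted as observed, the simplest approximation is a ratio of √0.9 = 0.95. Simulation with 10% dropout completely at random and compound symmetry true gave:

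- Single regression imputation: ratio 0.92 and type I error 6.6% (deterministic), 0.91 and 7.4% (stochastic).
- Last value carried forward: 0.99 and 4.8%.
- Multiple imputation with Rubin's rules: 1.01 and 5.2%.

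The complete-data run gave 0.98 and 5.8%, so part of the excess is simulation noise. Roughly 5% to 10% too small is a fair range for single regression-type imputation.

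**The case against.** The strongest reply is that the article states a random intercept but says nothing about the residuals. Compound symmetry follows only if they are independent with constant variance, and residual structure is a detail often left to an analysis plan. That stands as a caveat. Still, the random intercept is the only device the article names for within-woman correlation, and a reader would fit it in the default way.

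Second, no between-visit correlation or visit-specific SD is given, and the unequal intervals point mainly towards decay, which makes the test conservative. This is right. A reader might infer that the primary test is liberal, but the documents do not support a direction. Inflation needs T0–T1 to be clearly weaker than T1–T2, which is plausible if treatment reorders the women but is not shown.

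Third, a reader might infer that power falls below the planned 80%. That would need 2.61 to be the SD of the change, which the Sample Size section does not say. Read as a single-visit SD, power stays above 80% in both conservative cases worked here.

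Fourth, a reader might take "Missing data will be imputed and included in all analyses" to mean single imputation with filled values treated as observed. The article does not say so. Its method may stand in a fuller plan, and properly pooled multiple imputation shows no material distortion. The statement also covers the rank-sum tests of change scores, which do need complete data.

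Finally, if pain fails the normality check, the plan moves to those rank-sum tests, which do not use the pooled variance. The concern therefore applies when the mixed model is the analysis used.

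**Conclusion.** The point holds as a worthwhile improvement, not as a fatal flaw. The stated covariance device makes the precision of the primary T1 contrast depend on an assumption that the design gives reason to doubt. Over the correlations assumed here, the SE is between about 9% too small and 20% too large, with real two-sided type I error between about 7.4% and 1.9%. If compound symmetry holds, the error is zero. Only the SE, confidence interval and p-value are affected when data are complete, and the sample size of 108 stands. The imputation point is secondary: it matters only if a single-imputation method is used.

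**What to change.** In the primary mixed model, replace the random intercept with an unstructured covariance over T0, T1 and T2. Fit it by REML with Satterthwaite or Kenward-Roger degrees of freedom, as the software allows. Keep group, categorical time and group × time, and name the group contrast in T0-to-T1 change as the primary test.

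Fit this model to all observed visits without prior imputation, since the likelihood already uses partial records under missing at random. For analyses that need complete data, state multiple imputation with Rubin's rules. A delta-adjusted version could serve as a sensitivity analysis for dropout related to pain.

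The cost is a change of wording and one option in the SPSS mixed-model procedure. The covariance has six parameters instead of two, which is trivial with about 100 women. The article reports that data analysis has not started, so the change can still be prespecified.

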### Ethical Considerations

This project has been approved by the Ethics Committee for Drug Research of Navarra (PI_2023/81), and the necessary institutional authorization to carry out the study has been obtained . Participants will receive information about the project, their degree of involvement, and the legal requirements we will follow in an information sheet, as well as an informed consent form to be signed if they agree to voluntarily participate. Participants will not receive any compensation for participating in the study. The study will exhaustively comply with all the ethical-legal requirements in force related to research involving humans [47]. In order to maintain privacy and confidentiality, all data will be obtained under a personal and unique code. In the event that the IM-OA23 program is shown to be effective in improving pain, mobility, and lymphedema in breast cancer survivors, once the research is completed, breast cancer survivors from the CG will be invited to participate in the full program, and the resources used for the IG will be provided. In addition, the feasibility of incorporating the tool into the national health system will be assessed, with the aim of making it accessible to the entire population.

## Results

The intervention is expected to yield improvements in pain intensity, joint range, muscle strength, and symptoms associated with lymphedema, among other outcomes. The study was funded in December 2023. The number of participants recruited as of manuscript submission is approximately 80, and data analysis has not yet started. Data collection is expected to be finished by June 2026, and the results will be published in 2026.

## Discussion

### Expected Findings

This randomized controlled trial will investigate the potential effect of the combination of MI and AO therapies in improving the functionality of the affected upper limb in breast cancer survivors. Although previous studies have demonstrated the effectiveness of combining these therapies in improving pain, fear of movement, and other outcomes in conditions such as phantom limb syndrome, stroke, or chronic pain, no studies to date have examined their impact in female breast cancer survivors with upper-extremity symptoms. This study seeks to address that gap. Given the similarities of symptoms in breast cancer survivors to those observed in other conditions for which MI and AO therapies have proven effective, the potential benefits for quality of life and treatment appear promising.

### Implications for Clinical Practice

The results of this study have the potential to generate evidence supporting new therapeutic approaches for addressing functional limitations and mobility problems of the affected limb in women with breast cancer—a population in which these symptoms are common and frequently insufficiently treated.

This project is of particular interest given the growing number of female breast cancer survivors, many of whom face limitations in recovery and reintegration into daily activities due to disease-related consequences.

The implementation of the IM-OA23 program could directly benefit female breast cancer survivors with upper-limb sequelae. Aligned with current priorities for survivorship care outlined in the Strategic Framework of Primary and Community Care and the Comprehensive Plan of Care for Long-Term Cancer Survivors of the Spanish Society of Medical Oncology [48], the IM-OA23 program also represents an innovative approach with potential for significant social and economic impact nationally and internationally.

Short-term benefits may include improved pain management, increased mobility, and reduced lymphedema. If effective, the program could offer breast cancer survivors additional tools to alleviate pain and lymphedema while improving upper-limb mobility. This could reduce the need for pain medication and improve the ability to perform daily activities such as dressing, grooming, and reaching for objects while also helping prevent complications such as lymphedema-related infections.

Evaluating the medium-term impacts of the program would generate valuable knowledge on the translation of research into health care practice. Such assessments could clarify the program’s sustainability, its integration into clinical workflows, and its potential to inform evidence-based guidelines for survivorship care.

In the long term, the results of this study could have a significant impact on alleviating symptoms affecting the lives of breast cancer survivors. At the same time, it may contribute to improving the quality and continuity of survivorship care while offering a cost-effective tool to improve patient management and expand the resources available to health care professionals.

In addition, if effective, the program could be proposed as an open access resource at the international level—adapted into different languages—to be accessible not only to rehabilitation professionals but also directly to patients. Such an approach would facilitate global reach, allowing for its use from anywhere while enabling the monitoring of symptom evolution and adherence to the intervention and the timely resolution of emerging issues.

Finally, this study highlights the need to prioritize research on women and the health challenges they face. Beyond its immediate contributions, it has the potential to open new avenues for future research aimed at understanding and addressing symptoms that emerge with the chronification of specific pathologies.

### Study Limitations

This study has several limitations. First, the follow-up period of the intervention is short, restricted to 3 months. At this time point, the long-term effects of the intervention may not yet have fully emerged, potentially underestimating its sustained impact. However, it should be noted that the selected follow-up times are based on previous studies analyzing the combination of MI and AO therapies. It should also be noted that follow-up is constrained by the funding period and by the practical and organizational limitations of participants. Therefore, future research should include long-term evaluations of the intervention’s outcomes.

Second, given the behavioral nature of the program, it will not be possible to blind either the participants or the researchers delivering the intervention, which may introduce expectation bias. In addition, some outcomes (such as the number of repetitions and the frequency of exercises) rely on self-reported diaries, increasing the risk of reporting bias and raising potential concerns about adherence.

Third, the aim of the study is to evaluate the combination of MI and AO therapies, and although it would also be interesting to compare the effects of this combination with those of the therapies alone, due to the difficulty in recruiting volunteers, we will not be able to conduct a study in which we can compare the combination of MI and OA and the effects of the use of MI or OA alone.

### Conclusions

The implementation of an intervention based on MI and AO has the potential to positively impact female breast cancer patients who face physical and psychological sequelae that interfere with their daily lives. This study has the potential to contribute important evidence on the effectiveness of combining MI and AO while also offering pioneering insights into the implementation of these therapies within oncology. By extending the use of these therapies to breast cancer survivorship, the findings of this study could open up new avenues for innovative, nonpharmacological strategies to improve long-term care and quality of life in this growing patient population.
